### Qualitative interviews

At the end of the intervention (post 12 months), interviews will be undertaken with a sample of intervention participants, all intervention team leaders, and senior DHS management. The sample of intervention participants (a minimum of two from each intervention worksite) will be randomly selected from those who “opt-in” for this element on the final assessment questionnaire. The interviews will be semi-structured and delivered face-to-face by one research staff member. The interviews with participants and team leaders will include evaluation of the different intervention elements and adherence to the study site strategies identified and agreed upon within the group information session, as well as perceived organisational support for the key messages. The interviews with the senior management will also be semi-structured and delivered face-to-face, with the objectives being to canvass perspectives on the implementation of the intervention and next steps relating to the broader translation/dissemination of similar initiatives within the organisation.

### Economic evaluation

An economic evaluation will be undertaken alongside the trial to determine whether the intervention represents 'value-for-money’ measured against the control group (current practice). It will address issues of both technical efficiency ('how to do it’) through assessment of key design features of the intervention and the associated cost drivers, and allocative efficiency ('what to do’) through the modelling of longer term consequences and cost offsets. In addition to a 'trial-based evaluation’ (costs and outcomes exactly as per the trial), a 'modelled economic evaluation’ will also be undertaken, which extends the target population, time horizon and decision context.

### Feedback of study outcomes

Individual feedback on baseline patterns of sitting, standing and moving time both at the workplace and across all waking hours will be received by intervention participants as part of their one-on-one consultation to facilitate goal setting (Additional file 4: Figure S4). At the completion of both the 3- and 12-month assessments, all participants will receive individual feedback letters containing details of their average sitting, standing, and moving time (both at the workplace and overall) and their anthropometric and cardio-metabolic outcomes, including sex- and gender-specific reference/desirable ranges where applicable. This feedback will also include details of change from the previous assessment(s). Participants will be encouraged to consult their doctor to discuss any cardio-metabolic results outside the desirable range. To ensure participant safety, medical results requiring urgent attention will be communicated to the participant as soon as the health concern is identified.

### Sample size

Minimum differences of interest (MDI) for activity outcomes were 45 minutes of sitting, standing, prolonged sitting, and light activity, and 15 minutes of stepping and MVPA. Based on our study design, we expected an average of 20 participants/cluster, with strong clustering (ICC = 0.1; Design effect = 2.9) for activity (heavily influenced by workplace) and weak clustering (ICC = 0.01; Design Effect = 1.19) for the other outcomes (weakly influenced by workplace) with overall attrition of 30%. Standard deviations and pre-post correlations were assumed based on the earlier pilot [20].

Based on these assumptions, the sample size required to detect the MDI (45 min) for the primary outcome (workplace sitting, assumed SD = 70, pre-post correlation = 0.4) is 160 per group, spread across 8 clusters each. This sample size provides adequate power (≥90%) to detect minimum differences of interest on secondary workplace and overall activity outcomes, with assumed SDs and pre-post correlations (r) of 70–75 mins (r = 0.4) for sitting, standing and prolonged sitting; 20–35 minutes (r = 0.7) for stepping and MVPA; and, 60 minutes (r = 0.7) for light activity.

For the other secondary outcomes, minimum detectable differences (MDD) with 80-90% power were: 1.7-1.8 kg weight, 1.3-1.5 kg lean body mass and fat mass, 1.5-1.7 cm waist circumference, 5–6 mmHg systolic blood pressure, 4 mmHg diastolic blood pressure, 11–13 pmol insulin, 0.28-0.33 mmol/L glucose, 0.24-0.25 /0.19-0.22 / 0.10-0.11 mmol/L total / LDL- / HDL- cholesterol, 0.12-0.14 mmol/L log triglycerides, 0.3-0.4 units work performance, 0.3-0.4 units eyestrain, 0.6-0.7 units fatigue. Based on these MDDs, power would be adequate to detect effect sizes of the magnitude observed in the pilot study [20] for glucose (0.3 mmol/L), insulin (15.7 pmol) log triglycerides (0.19 mmol/L) and diastolic blood pressure (4.0 mmHg) only.

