### Statistical analyses

In accordance with the study aims, statistical analyses will be conducted to determine whether the intervention group differs from the control group in changes over time in primary and secondary outcomes. Statistical significance will be set at the conventional 5% level (two-tailed). Consistent with the cluster-randomised design, and in order to examine both workplace-level and individual-level variation, Linear Mixed Models will be used (SAS version 9.3 or STATA version 12). These models will use random intercepts for workplace and individuals (to account for clustering within workplaces and repeated measures) and will adjust for baseline values and potential confounders. Appropriate distributions (e.g., normal, gamma, binomial) and links (e.g., identity, log) will be used depending on the distribution of the data. *Potential confounders* will initially be identified *a priori* based on the findings of our preceding epidemiological studies and the relevant research literature, and will be controlled via statistical adjustment as relevant to each specific outcome should they display association with the outcome (significant at p < 0.2). Analyses will follow intention-to-treat principles. Assumptions will be tested regarding missing data, randomisation, and contamination (an important consideration given that the study sites are all within the one organisation). Contamination will be assessed by tracking individuals within study sites (i.e. transfers to a study site of the same allocation, no allocation or opposite allocation) and by assessing, at the end of the program, self-reported use of specific intervention strategies to reduce prolonged sitting.

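### The blanket claim of at least 90% power for the secondary activity outcomes does not follow from the protocol's own inputs at the upper SDs (about 75–84% for stepping/MVPA at SD 35), and two minimum-detectable-difference ranges are internally inconsistent

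*Protocol article*

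**What the plan says.** All of the figures are in the Sample size section of the protocol article.

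- The minimum differences of interest are "45 minutes of sitting, standing, prolonged sitting, and light activity, and 15 minutes of stepping and MVPA".
- Clusters average 20 participants, "with strong clustering (ICC = 0.1; Design effect = 2.9) for activity", with overall attrition of 30%.
- For the primary outcome ("workplace sitting, assumed SD = 70, pre-post correlation = 0.4") the required size "is 160 per group, spread across 8 clusters each". No power is printed for this outcome.
- For the secondary activity outcomes the section says: "This sample size provides adequate power (≥90%) to detect minimum differences of interest on secondary workplace and overall activity outcomes".
- The SDs that this claim covers follow in the same sentence. One entry reads "20–35 minutes (r = 0.7) for stepping and MVPA". The three posture outcomes (total sitting, prolonged sitting, standing) have SDs of 70 to 75 minutes with a correlation of 0.4. Light activity has an SD of 60 minutes with a correlation of 0.7.
- For the other outcomes it gives minimum detectable differences at 80–90% power, among them "1.7-1.8 kg weight" and 0.24–0.25 mmol/L for total cholesterol.

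The Statistical analyses section sets a two-sided 5% level and a linear mixed model adjusted for baseline.

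**The concern.** The power sentence attaches one figure, at least 90%, to every secondary activity outcome over its whole listed SD range. Attrition and clustering act alike on all activity outcomes, so what separates them is the difference of interest divided by the baseline-adjusted SD. That ratio is clearly smaller for stepping/MVPA at SD 35 than for the primary outcome, which makes a common 90% doubtful before any further calculation.

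Stepping, MVPA, standing and prolonged sitting are named activity outcomes. A null result on stepping or MVPA would be read against a printed type II error of at most 10%. If the SD is near the protocol's own upper value, the true figure is 16–25%.

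The minimum detectable differences raise a separate question. With all other inputs fixed, the 80% and 90% values stand in a constant ratio, and two of the printed ranges look too narrow for it.

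**Working it through.** **Inputs** (Sample size section unless noted): 160 per group in 8 clusters; 20 per cluster; ICC 0.1; 30% attrition; the differences, SDs and correlations listed above. From Statistical analyses: two-sided 5%, baseline adjustment.

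**Design effect.** 1 + (20 − 1) × 0.1 = 2.9, which reproduces the printed figure. That uses cluster size before attrition. After attrition a cluster holds 20 × 0.7 = 14, giving 1 + 13 × 0.1 = 2.3. The article does not say which applies to the analysed sample, so both are carried.

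**Effective n per group.** Analysed: 160 × 0.7 = 112.
- 112 / 2.9 = 38.6
- 112 / 2.3 = 48.7
- attrition ignored: 160 / 2.9 = 55.2

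**Can 160 be reproduced for the primary outcome?** At 90% power, n = 2 × (1.960 + 1.2816)² × 70² × (1 − 0.4²) / 45² = 42.7 per group before inflation.
- × 2.3 / 0.7 = 140.3, so 141. That is just over 7 clusters of 20, hence 8 clusters and 160.
- × 2.9 / 0.7 = 177.

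So 160 is attainable at 90% on one reasonable convention.

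**Power**, one follow-up, normal approximation: Φ(δ / SE − 1.96), with SE = √(2 × SD² × (1 − r²) / n_eff).

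For stepping/MVPA at SD 35, r = 0.7, the adjusted SD is 35 × √0.51 = 25.0.
- n_eff 38.6: SE 5.69; 15 / 5.69 = 2.64; power 75.1%
- n_eff 48.7: SE 5.07; 15 / 5.07 = 2.96; power 84.2%
- n_eff 55.2: SE 4.76; 15 / 4.76 = 3.15; power 88.3%

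| Outcome, difference | SD, r | Design effect 2.9 | Design effect 2.3 |
|---|---|---|---|
| Sitting (primary and secondary), standing, prolonged sitting, 45 min | 70, 0.4 | 86.9% | 93.3% |
| Sitting, standing, prolonged sitting, 45 min | 75, 0.4 | 82.0% | 89.8% |
| Stepping/MVPA, 15 min | 20, 0.7 | 99.6% | 99.9% |
| Stepping/MVPA, 15 min | 30, 0.7 | 86.8% | 93.3% |
| Stepping/MVPA, 15 min | 35, 0.7 | 75.1% | 84.2% |
| Light activity, 45 min | 60, 0.7 | 99.6% | 99.9% |

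The difference detectable with 90% power at SD 35 is 3.2415 × SE: 3.2415 × 5.69 = 18.4 min at 2.9, and 3.2415 × 5.07 = 16.4 min at 2.3. With attrition, the largest SD that keeps 90% for 15 minutes is 28.5 at 2.9 and 32.0 at 2.3. A change-score analysis does worse at SD 35: 68.1% and 77.9%.

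**A check free of attrition and design effect.** The difference over the adjusted SD is 45 / (70 × √0.84) = 0.701 for the primary outcome and 15 / (35 × √0.51) = 0.600 for stepping/MVPA at SD 35. The second therefore needs (0.701 / 0.600)² = 1.37 times the sample of the first.

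**Minimum detectable differences.** With other inputs fixed, the 90% value divided by the 80% value is (1.960 + 1.2816) / (1.960 + 0.8416) = 1.157, whatever the SD, ICC or attrition. The largest ratios that rounding allows are:
- weight 1.7–1.8 kg: 1.85 / 1.65 = 1.12
- total cholesterol 0.24–0.25 mmol/L: 0.255 / 0.235 = 1.085

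Neither reaches 1.157. Other printed ranges do fit, for example LDL cholesterol (0.22 / 0.19 = 1.158). If the lower figures are right, the 90% values would be about 1.7 × 1.157 = 1.97 kg and 0.24 × 1.157 = 0.28 mmol/L. If the upper figures are right, the 80% values would be about 1.8 / 1.157 = 1.56 kg and 0.25 / 1.157 = 0.22 mmol/L.

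**The case against.** The strongest defence is that the printed design effect of 2.9 belongs to 20 per cluster, before attrition, so applying it to 112 completers mixes two stages and is conservative. This stands in part. At 2.3 the sitting, standing and prolonged-sitting outcomes reach about 90–93%, so their shortfall is conditional. It does not rescue stepping/MVPA at SD 35, which stays at 84%.

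A second defence is that the planned mixed model uses repeated measures and there are two follow-ups. Averaging both, under an assumed compound-symmetry correlation of 0.7, gives about 88% at 2.9 and 94% at 2.3 for SD 35. One therefore cannot say that the figure fails under every conceivable reading. But the article states neither that averaging nor that correlation as the basis for its power. No single-follow-up variant examined reaches 90%.

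Third, the failure is confined to the top of the range: SD 20 gives over 99% and SD 30 gives 87–93%. That is true, but the sentence claims 90% for the whole range.

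Three stronger readings are tempting and not supported:
- A reader might infer that 160 per group is wrong for the primary outcome. No power is printed for it, 160 can be reached as shown, and its power is 87–93% over the same two design effects.
- A reader might infer that attrition was applied as a multiplier of 1.3, since 42.7 × 2.9 × 1.3 = 161. That coincidence does not show what was done.
- A reader might infer that the weight and cholesterol ranges overstate what the trial can detect. Without SDs and correlations for these outcomes, either endpoint could be the wrong one, and the error could run the other way.

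**Conclusion.** The concern holds for the secondary power statement and for the two ranges. On the article's own inputs, at least 90% is not attained for 15 minutes of stepping/MVPA at SD 35: power is about 75% (design effect 2.9) to 84% (2.3). For sitting, standing and prolonged sitting the statement fails at 2.9 and holds, to rounding, at 2.3. For light activity and for stepping/MVPA at the low end of the SD range it is correct. The power figures assume a normal approximation, one follow-up, variance reduction by 1 − r² from baseline adjustment, and the stated 30% attrition.

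The weight and total-cholesterol ranges cannot be 80% and 90% values of the same calculation. The discrepancy is small, and the article does not show which end is off.

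This is a minor correction to stated properties of secondary outcomes. It does not call the sample size, design or analysis into question.

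**What to change.** Keep 160 per group and revise the wording of the Sample size section.

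1. Replace the blanket 90% with outcome-specific power: about 75–84% for stepping/MVPA at SD 35, 82–90% for sitting, standing and prolonged sitting at SD 75, and over 99% for light activity. Alternatively, give the difference detectable with 90% power at SD 35 as about 16–18 minutes.
2. Say which design effect applies after attrition, and give the primary-outcome power on that basis: 87% at 2.9 or 93% at 2.3. Once this is chosen, each range in item 1 becomes a single figure.
3. If the power was meant to rest on both follow-ups jointly, say so and give the assumed correlation between them.
4. Recompute the weight and total-cholesterol ranges from their SDs and correlations.

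The cost is a few sentences. Recruitment, design and analysis are unchanged, and the stated power for some secondary outcomes becomes less favourable.

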### Statistical analyses

In accordance with the study aims, statistical analyses will be conducted to determine whether the intervention group differs from the control group in changes over time in primary and secondary outcomes. Statistical significance will be set at the conventional 5% level (two-tailed). Consistent with the cluster-randomised design, and in order to examine both workplace-level and individual-level variation, Linear Mixed Models will be used (SAS version 9.3 or STATA version 12). These models will use random intercepts for workplace and individuals (to account for clustering within workplaces and repeated measures) and will adjust for baseline values and potential confounders. Appropriate distributions (e.g., normal, gamma, binomial) and links (e.g., identity, log) will be used depending on the distribution of the data. *Potential confounders* will initially be identified *a priori* based on the findings of our preceding epidemiological studies and the relevant research literature, and will be controlled via statistical adjustment as relevant to each specific outcome should they display association with the outcome (significant at p < 0.2). Analyses will follow intention-to-treat principles. Assumptions will be tested regarding missing data, randomisation, and contamination (an important consideration given that the study sites are all within the one organisation). Contamination will be assessed by tracking individuals within study sites (i.e. transfers to a study site of the same allocation, no allocation or opposite allocation) and by assessing, at the end of the program, self-reported use of specific intervention strategies to reduce prolonged sitting.

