**Methods/Design:**

A two-arm cluster-randomized controlled trial (RCT), with worksites as the unit of randomization, will be conducted in 16 worksites located in Victoria, Australia. Work units from one organisation (Department of Human Services, Australian Government) will be allocated to either the multi-component intervention (organisational, environmental [height-adjustable workstations], and individual behavioural strategies) or to a usual practice control group. The recruitment target is 160 participants (office-based workers aged 18–65 years and working at least 0.6 full time equivalent) per arm. At each assessment (0- [baseline], 3- [post intervention], and 12-months [follow-up]), objective measurement via the activPAL3 activity monitor will be used to assess workplace: sitting time (primary outcome); prolonged sitting time (sitting time accrued in bouts of ≥30 minutes); standing time; sit-to-stand transitions; and, moving time. Additional outcomes assessed will include: non-workplace activity; cardio-metabolic biomarkers and health indicators (including fasting glucose, lipids and insulin; anthropometric measures; blood pressure; and, musculoskeletal symptoms); and, work-related outcomes (presenteeism, absenteeism, productivity, work performance). Incremental cost-effectiveness and identification of both workplace and individual-level mediators and moderators of change will also be evaluated.

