### Randomisation

Randomisation to either the intervention or control arms of the trial will be at the level of the study site. Simple cluster randomisation will be achieved by generating a randomisation plan for up to 24 clusters/worksites in one block (http://www.randomization.com). Participating sites will subsequently be randomly matched against the randomisation plan using a list randomiser (http://www.random.org). This method allows study staff to implement the study intervention and control protocols in an order consistent with logistical capacity. Study sites will be enrolled and then randomized until the required number of clusters and sample size is reached.

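### The p < 0.2 outcome screen lets the trial data choose the primary model, and can distort the result if candidate covariates vary mainly between the 16 sites

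*Protocol article*

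**What the plan says.** The protocol article, Statistical analyses, sets the test: "Statistical significance will be set at the conventional 5% level (two-tailed". On the model it says "Linear Mixed Models will be used (SAS version 9.3 or STATA version 12", and "These models will use random intercepts for workplace and individuals", with adjustment for baseline values and potential confounders. Candidate confounders are to be identified beforehand, "based on the findings of our preceding epidemiological studies and the relevant research literature". Each is then adjusted for, outcome by outcome, "should they display association with the outcome (significant at p < 0.2".

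The section does not say whether arm is in the screening model, whether any candidate is a site characteristic, or which reference distribution the final test uses. On the design, the Abstract says the trial "will be conducted in 16 worksites located in Victoria, Australia", and the Randomisation section says "Randomisation to either the intervention or control arms of the trial will be at the level of the study site".

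**The concern.** The candidates are chosen in advance, but which of them stay is decided by the outcome. This is a stated rule, so a later analysis plan would have to overturn it rather than fill a gap.

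With only 16 randomised units, and simple cluster randomisation with no strata described, a characteristic that varies between sites can easily be unbalanced between arms by chance. Two different problems can then follow, depending on how the screen is run:

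- **Arm left out of the screen.** A covariate that happens to line up with arm picks up the treatment effect, passes the screen for that reason, and then absorbs part of the effect.
- **Arm included.** The screen favours covariates that happen to explain chance differences between sites. The estimated between-site variance comes out too small, and so does the standard error.

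At stake are the accuracy of the primary estimate under the first reading and the 5% error rate under the second.

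**Working it through.** **Inputs from the protocol article (Sample size).** "workplace sitting, assumed SD = 70, pre-post correlation = 0.4) is 160 per group, spread across 8 clusters each". The same section gives a difference of interest of 45 min, an average of 20 participants per cluster, ICC 0.1, design effect 2.9 and 30% attrition.

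**Reproducing the plan's own figure.** Design effect = 1 + (20 - 1) x 0.1 = 2.9. The power behind the primary figure is not stated, but two ordinary routes come within 3% of 160 per group:

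- 80% power, ignoring the pre-post correlation: 2 x (1.960 + 0.842)^2 x 70^2 / 45^2 x 2.9 / 0.7 = 157.4, which is 8 clusters of 20.
- 90% power, with variance factor 1 - 0.4^2 = 0.84 and attrition applied as x 1.3: 2 x (1.960 + 1.282)^2 x 70^2 / 45^2 x 0.84 x 2.9 x 1.3 = 161.0.

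The design figures are coherent and serve as the basis of the simulation.

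**Simulation.** 8 v 8 sites; 20 x 0.7 = 14 completers per site; SD 70; ICC 0.1; baseline correlation 0.4; one follow-up; REML random-intercept model; 6,000 trials per scenario (Monte Carlo SE about 0.2 min for the estimate and 0.3 points for a 5% rejection rate). Candidates were screened one at a time at p < 0.2.

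Assumed, because the article does not give them: 6 to 8 individual-level candidates (half prognostic, coefficient 0.15 SD, covariate ICC 0.05), plus 0, 1, 2 or 4 site-level candidates unrelated to outcome. The final test is t on 14 df less the number of selected site-level covariates. Figures in brackets are from a separate cluster-level check.

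| Site-level candidates | Arm omitted: change in a true 45 min | Arm omitted: power, baseline-only model to screened model | Arm included: size of the 5% test |
|---|---|---|---|
| 0 | -0.2 | 87.0% to 88.3% | 5.1% |
| 1 | -0.9 (-0.8) | 87.9% to 87.0% | 6.0% (5.0%) |
| 2 | -2.2 (-1.4) | 87.2% to 84.3% | 6.7% (6.5%) |
| 4 | -3.3 (-2.9) | 87.2% to 81.0% | 6.9% (7.9%) |

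The changes are the simulated bias in SD units times 70; for four candidates, -0.0478 x 70 = -3.3.

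- **Arm omitted, no true effect, four site-level candidates:** size 4.6%, so no excess of false positives.
- **Arm included, true 45-min effect, four site-level candidates:** bias 0.0038 x 70 = 0.3 min, within Monte Carlo error.

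**What drives the harm.** A further run used eight non-prognostic individual-level candidates, no site-level ones, and 3,000 trials per scenario. At covariate ICC 0.05 almost nothing changed (44.6 min; size 5.1%). At ICC 0.5 the estimate was 42.9 min with arm omitted, and size was 6.7% (t on 14 df) with arm included. At ICC 0.9 the figures were 40.0 min and 8.8%. So the condition is clustering of the candidates by site. Eight candidates all at ICC 0.9 is an upper case, not an expectation.

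**After the fix.** With every candidate kept and no screen, the reduced-df t test rejected 4.4% to 5.3% under the null, and bias was within Monte Carlo error. Eight fixed individual-level covariates gave 88.5% power. Six individual-level and four site-level covariates gave 73.7%, which is why site-level covariates should be few.

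**The case against.** The strongest objection is that the harm is conditional. The article names no site-level confounder. Where it does name workplace features such as office layout, it lists them as moderators. If every candidate is an individual-level factor with weak clustering, the screen neither biases the estimate nor inflates the test. This stands, and a reader who inferred that the screen necessarily spoils the primary result would go beyond the documents. It does not remove the point: site-clustered candidates are not excluded either, and they are plausible. Under Recruitment of study sites, a site normally contributes one working team, so job-related variables may hardly vary within a site.

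Three further limits also stand:

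- The two harms belong to alternative readings of the screen. They cannot both apply to the same analysis.
- A reader might infer that the test also exceeds 5% because a large-sample z test is used. The article states no z test, and the choice of degrees of freedom is commonly left to the analysis plan. The 1.96 cut-off on 14 df has true size 7.0% with no screening at all, so that is a separate matter. Nor do small-sample degrees of freedom rescue the screened test: the sizes in the last column of the table already use them.
- Different covariates for different outcomes are not a defect in themselves. Sitting time and insulin can have different predictors.

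**Conclusion.** The point holds in conditional form. The rule makes the primary model depend on the trial's outcome data, which is avoidable. Whether it distorts the result depends on facts that the article leaves open: whether arm is in the screen, and how many candidates vary mainly between sites.

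With one to four site-level candidates the plausible cost is about 1 to 3 minutes of a 45-minute effect (2% to 7%) with some loss of power, or a true test size of about 5-6% rising to 7-8%. With weakly clustered candidates the cost is nil. These figures rest on the assumed number and strength of candidates, equal cluster sizes, normal outcomes and a single follow-up, whereas the protocol's model also has repeated measures within individuals. The direction is firm; the exact percentages are not. Severity: should be fixed before analysis. The documents do not support calling the primary test invalid.

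**What to change.** Before any outcome data are seen, name the covariates of the primary model and keep them regardless of p-value: arm, the baseline value of the outcome, and a short list of prognostic individual-level factors (age and gender, for example), with few or no site-level covariates. Sets may differ between outcomes if each is fixed in advance. Report the p < 0.2 model only as a sensitivity analysis, and state whether arm is in its screen.

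As a companion to the fixed set, test the arm effect with a small-sample reference distribution suited to 16 sites, such as Kenward-Roger or t on 14 df less any site-level covariates.

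The cost is a change of wording. Intervals would be slightly wider than large-sample ones: 2.145 / 1.960 = 1.094, about 9% on 14 df.
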